## Discussion

Understanding and measuring empathy has broad implications, impacting mental health interventions, VR design, and empathy training. Measuring empathy deficits in psychiatric disorders with models such as we plan to build can be used to initiate, monitor, and adapt therapeutic interventions. VR, as the “ultimate empathy machine,” can transform empathy training in healthcare, education, and other contexts by immersing individuals in lifelike scenarios, and our models can again be used for monitoring and guiding the training. This way, it can more successfully challenge preconceptions, foster perspective-taking, and enhance empathic abilities. The ability to measure empathy can also be used in entertainment, to adapt VR content so that the user experiences it more fully, develops stronger (or weaker, as desired) feelings for virtual characters, and similar. All this can also contribute to personal growth and self-awareness, emphasizing empathy as a valuable skill.

This research endeavors to establish a “golden standard” for measuring empathy as a primary outcome. Additionally, it aims to differentiate the impact of various emotions on physiological attributes, identify the emotion that elicits the most intense empathic response from participants, explore potential gender differences in the intensity and general nature of responses, and investigate whether emotions expressed with narratives or without content exert a stronger influence on empathic responses.

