## Abstract

Virtual reality (VR) technology is often referred to as the ‘ultimate empathy machine’ due to its capability to immerse users in alternate perspectives and environments beyond their immediate physical reality. In this study, participants will be immersed in 3-dimensional 360° VR videos where actors express different emotions (sadness, happiness, anger, and anxiousness). The primary objective is to investigate the potential relationship between participants’ empathy levels and the changes in their physiological attributes. The empathy levels will be self-reported with questionnaires, and physiological attributes will be measured using different sensors. The main outcome of the study will be a machine learning model to predict a person’s empathy level based on their physiological responses while watching VR videos. Despite the existence of established methodologies and metrics in research and clinical domains, our aim is to contribute to addressing the gap of a universally accepted “gold standard” for assessing empathy. Additionally, we expect to deepen our understanding of the relationship between different emotions and psychological attributes, gender differences in empathy, and the impact of narrative context on empathic responses.

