
The choice of measurement depends on the specific research objectives, population under study, and the dimensions of empathy being assessed. It is important to consider that each measurement method has its strengths and limitations. To combat the limitations, researchers often use multiple measures in combination to capture the different facets of empathy comprehensively. This increases the complexity of measuring empathy, even though some individual measures are already complex and time consuming. Ideally we would like a measure of empathy that is reasonably objective and can be while applied during arbitrary tasks (i.e., it does not require the performance of a specific task). Psychophysiological measures satisfy these requirements best, the precise connection between these measures and empathy remains an open question. Our study aims to aims to bridge this gap by developing a powerful machine learning model that directly measures empathy based on physiological signals, offering a novel and more targeted perspective on empathetic responses.

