
The aim of this study is to research how the empathy of the participants is related to changes in their physiological attributes measured by different sensors (inertial measurement unit, photoplethysmogram, eye tracking, electromyography (EMG), electrodermal activity, 3-axis accelerometer). Using a VR headset, the participants are going to be immersed in 3-dimensional 360° videos of actors who express different emotions (sadness, happiness, anger and anxiousness). They will report their experience of empathy through short questionnaires. Based on their sensor and questionnaires data, a machine learning model will be developed that will predict a person’s score on an empathy questionnaire based on their physiological arousal while watching VR videos.

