### Data analysis

In order to process the collected data effectively, several steps will be taken. Firstly, the derived features obtained from each module of the Emteq Emotion AI Engine, as well as the features from the Empatica E4, will be combined by concatenating the data files. The epoch timestamps will then be converted to human-readable date and time formats, and the output labels will be populated based on the scores from the empathy questionnaires. The classification task will involve multi-label classification, with the affective component of trait empathy and state empathy serving as the labels of interest.

If a variable has a modest amount of missing values, imputation will be used. Otherwise, if the amount is substantial, the corresponding data will be dropped. The derived features are provided by different devices with data updated at different intervals, ranging from 10 seconds to 500 milliseconds, resulting in varying data frequencies. Undersampling or oversampling will be used to handle the high or the low frequency of the derived features accordingly, and they will be aligned at a consistent interval. Regarding the variables, while some are ready to be used, as the derived features are, from others, such as the raw sensor data, we will extract features.

The research aims to address several key questions. Firstly, it seeks to explore the connection between physiological attributes and empathy. For this purpose we will use multiple standard machine learning classifiers to develop prediction models, with different parameters tested to optimize performance. The predictive models will be developed based on the descriptive space consisting of physiological data from the sensors and data from the questionnaires. Additionally, personalized models will be explored to enhance predictions. Personalized feature values will be utilized, employing normalization techniques by calculating the ratio between the parameter value and the average value for each participant over the entire viewing period. If the initial results prove unsatisfactory, deep learning techniques will be applied directly to the raw sensor data, bypassing the use of the derived features provided by Emteq. Furthermore, we will explore deep learning approaches using the derived features, allowing us to consider both options.

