In statistical modeling, established methodologies exist to calculate the required sample size for achieving model stability. However, in the context of utilizing machine learning models, it is challenging to precisely determine the optimal sample size. For our study, we anticipate that approximately 100 participants will suffice to develop a stable predictive model. While we cannot determine this with certainty beforehand due to the complexities of machine learning algorithms, it is worth noting that previous studies [34, 37–40, 69] have successfully developed stable models using even smaller sample sizes. Based on this precedent, we believe that our chosen sample size will be adequate for the purposes of our investigation.

While convenient for logistical reasons, our use of convenience sampling introduces potential limitations. In employing this method, our sample may not be fully representative of the broader population due to potential biases associated with self-selection. This could limit the generalizability of our findings beyond the specific group of individuals who volunteered or were readily available. Nevertheless, the practicality of this approach expedites participant recruitment, allowing for extensive data collection in a controlled laboratory setting. Despite acknowledged limitations, we believe our targeted investigation will yield valuable insights into the relationships between empathy, physiological attributes, and immersive VR experiences within the context of our specific sample.

One of the primary challenges encountered in studies of this nature lies in establishing a reliable ground truth. We plan to do this with questionnaires. However, it is important to acknowledge that participants grading their own empathic states may introduce errors in the form of subjective biases. In light of this consideration, we will use two distinct questionnaires, one for measuring state empathy and another for trait empathy. This approach aims to minimize potential errors in our measurements in a way that may reveal some pattern of connections between the two.

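### The Discussion makes a reference standard for empathy a primary outcome, but the only criterion is self-report, so the design can show only how well self-reported empathy is predicted

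*Protocol article*

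**What the plan says.** **The claim.** The protocol article's Discussion states: "This research endeavors to establish a “golden standard” for measuring empathy as a primary outcome". The Introduction, after reviewing ways to measure empathy, describes the project as "developing a powerful machine learning model that directly measures empathy based on physiological signals".

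**The criterion.** The aim paragraph of the Introduction says "a machine learning model will be developed that will predict a person’s score on an empathy questionnaire". Data analysis says "the output labels will be populated based on the scores from the empathy questionnaires", "with the affective component of trait empathy and state empathy serving as the labels of interest". Under VR sessions, trait empathy comes from the QCAE, and state empathy from three affective items of a state empathy scale, answered after each emotion. Both are self-report. Strengths and limitations confirms that questionnaires supply the ground truth.

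**The admitted weakness.** The Introduction lists social desirability and inaccurate self-assessment among the possible limits of self-report. Strengths and limitations says of this study that "participants grading their own empathic states may introduce errors in the form of subjective biases". The response is to use one state and one trait questionnaire: "This approach aims to minimize potential errors in our measurements in a way that may reveal some pattern of connections between the two".

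**The modest aims.** The Abstract says "our aim is to contribute to addressing the gap of a universally accepted “gold standard” for assessing empathy" and gives the primary objective as a possible relationship between self-reported empathy and physiology. Study design and study population (Recruitment) calls the study correlational, with an association as its primary objective.

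**The concern.** A reference standard is a measure against which others are judged. To support that claim, a study needs some evidence on the new measure that does not come from the measure it was trained to reproduce. Here success can only mean agreement with a self-rating. The article describes performance tasks and behavioural observation in the Introduction but uses neither as a criterion.

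What is at stake is the conclusion the study may draw. A well-performing model would carry over whatever response bias the questionnaires contain, and could still be reported as an objective reference. The article attaches uses to such a model: the Introduction mentions selecting people for roles that need empathy, and the Discussion mentions starting, monitoring and adapting therapy. A reader who met the Discussion alone would take the outcome to be something the design does not deliver.

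**Working it through.** The plan gives no figure on this point, so there is none to reproduce. The check is a comparison of the text, followed by two illustrations with assumed values.

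**1. Is there any criterion other than self-report?**

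| Element (VR sessions, Data analysis) | Role | Independent empathy criterion? |
|---|---|---|
| QCAE, affective component | Label | No, self-report |
| Three state empathy items | Label | No, self-report |
| SAM arousal and valence | Self-rating of affect | No |
| One personal distress item | Self-rating | No |
| Roller coaster video | Non-empathic arousal control | No |

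The last three rows help to separate empathic from general arousal. None says whether a person scored as empathic is so. Data analysis also places questionnaire data among the predictors, so a model built that way is not purely physiological.

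**2. What does agreement with the questionnaire tell us about empathy?**

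Let E be true empathy, Q the questionnaire score and M the model output. Let r = corr(Q, E), which the study cannot observe, and m = corr(M, Q), which it can. For the three correlations to be jointly possible, the determinant of their matrix must not be negative:

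1 + 2·r·m·x − r² − m² − x² ≥ 0, where x = corr(M, E).

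Solving for x, it lies within r·m ± √((1 − r²)(1 − m²)).

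- r = 0.7, m = 0.5: 0.35 ± √(0.51 × 0.75) = 0.35 ± 0.618, that is −0.27 to 0.97.
- r = 0.7, m = 0.9: 0.63 ± √(0.51 × 0.19) = 0.63 ± 0.311, that is 0.32 to 0.94.
- r = 0.9, m = 0.5: 0.45 ± √(0.19 × 0.75) = 0.45 ± 0.377, that is 0.07 to 0.83.
- m = 1: the root is zero and x = r exactly.

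In the first two cases the range runs both above and below the questionnaire's own 0.7. In the third it lies wholly below 0.9. With perfect agreement the model is as valid as the questionnaire and no more. Over r of 0.5, 0.7 and 0.9 and m from 0.3 to 1, no combination guarantees that the model is the better measure. Since r is unobserved, the study cannot tell which case applies.

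**3. Does a second questionnaire minimise the error?**

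Take a version generous to the plan, in which both questionnaires measure the same construct: Q_i = E + B + e_i, with B a bias shared by self-reports. Assume Var(E) = 1, Var(B) = 0.5 and Var(e) = 0.5. The mean of k questionnaires correlates with E at 1/√(1 + 0.5 + 0.5/k):

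- k = 1: 1/√2 = 0.707
- k = 2: 1/√1.75 = 0.756
- k without limit: 1/√1.5 = 0.816

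Random error averages out; shared bias does not. Nor does agreement between the two reveal the bias. Their correlation is (1 + Var(B))/(1 + Var(B) + Var(e)), which is 1.5/2 = 0.75 with the shared bias and 1/1.5 = 0.667 without it. Yet the validity of one questionnaire is 0.707 with the bias and 1/√1.5 = 0.816 without it. The biased pair agrees better and measures worse.

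In this study the position is less favourable still. One questionnaire measures trait and the other state, so disagreement may be a true difference and agreement may be response style. The plan also treats them as separate labels and does not average them.

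**The case against.** The strongest reply is that the operational aim is already modest. The Abstract speaks of contributing to a gap, the Introduction of predicting a questionnaire score, and the study design section of an association. The Discussion sentence is worded as an endeavour. The authors name ground truth as a main challenge, say openly that self-rating may err, and hedge their remedy. The roller coaster control, the SAM ratings and the distress item show care about what the sensors pick up. The uses in selection and therapy are described as future possibilities.

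Much of this stands. It means that the defect lies in the claim, and that the data collection need not change. It does not remove the defect: the Discussion still names the reference standard as a primary outcome without qualification, at odds with three other places in the same article, and the remedy offered does not deal with shared bias. Nor is this a detail for an analysis plan, because the article itself fixes both the claim and the criterion.

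Some stronger readings are tempting but unsupported:

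- A reader might infer that the plan claims the model will outperform the questionnaire. It never says so; the Introduction argues for objectivity and for freedom from a specific task.
- A reader might infer that the plan concedes its criterion is biased. It says only that it may be.
- A reader might expect the model to inherit a reporting bias that differs by gender, or to share some stated fraction of variance with true empathy. The documents give no basis for either.

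**Conclusion.** The point holds as a mismatch between the stated primary outcome and what the design can establish. The study can estimate how well predictions reproduce self-reported affective trait empathy and state empathy. It cannot establish a reference standard or show that empathy is measured directly. The sentence suggesting that two questionnaires minimise error is not right for bias shared by self-reports.

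The documents allow no numerical size. The ranges in the working depend on assumed correlations and variances and serve only to show the logic. The conclusion rests on the article's own statement of its labels, and on the absence of any empathy criterion other than self-report. The study remains worth doing under its modest aim; what changes is the conclusion it may draw.

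**What to change.** 1. In the Discussion, restate the primary outcome as out-of-sample prediction of self-reported affective trait empathy and self-reported state empathy. This agrees with the Abstract, the aim paragraph of the Introduction, and Study design and study population (Recruitment). Name the affective component, since the full QCAE score is not the label.
2. Report a sensor-only model separately from any model that also uses questionnaire predictors, so that a reader can see what physiology alone contributes.
3. Remove the golden standard as an outcome from the Discussion, and remove the claim of direct measurement from the Introduction.
4. In Strengths and limitations, replace the statement about minimising error. Say instead that both questionnaires can share self-report bias and that the correlation between them is descriptive only.

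The cost is a less ambitious claim and slightly more analysis work for the separate sensor-only report. No new data are needed.

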### Strengths and limitations

Through this research, we aim to gain a comprehensive understanding of the potential outcomes and the potential directions that further research in this field could take. However, it is important to recognize specific limitations in addition to the potential listed findings. The sensors we will use are not feasible for everyday use, and consequently neither can the method for measuring empathy we plan to develop. Nevertheless, it can be used in VR, and measuring empathy in VR is particularly valuable since VR technology is often referred to as the ‘ultimate empathy machine.’ One limitation pertains to the study’s suitability for laboratory conduction rather than real-world investigation. As a result, the measures obtained may not fully represent naturalistic empathic responses.

There remains a possibility that participants exposed to the narrative versions may be influenced by the specific storyline. Similarly, participants watching the non-narrative versions could also be influenced by the actors’ portrayals, potentially limiting the study’s generalizability. To mitigate this potential influence from the particular scenario, variations in the narratives have been introduced. Additionally, an extra version without narratives has been included. This indicates our conscientious effort to evoke empathy in a highly realistic manner and devise the most comprehensive procedure feasible.

While our intent is to deeply immerse participants and mitigate factors that could disrupt this immersion, certain considerations must be made. Specifically, the presence of facial sensors on the VR headset leads to the exclusion of participants who wear glasses. Consequently, our method potentially limits the inclusion of older individuals in the sample. Since the study is expected to primarily involve a younger population aged 18 and above, there might be physiological attribute variations and distinct responses to empathy scenarios among older individuals that will not be adequately represented in our sample size. As a result, the study’s scope may be limited concerning the generalization of findings to the broader population, particularly in regards to older age groups.

In statistical modeling, established methodologies exist to calculate the required sample size for achieving model stability. However, in the context of utilizing machine learning models, it is challenging to precisely determine the optimal sample size. For our study, we anticipate that approximately 100 participants will suffice to develop a stable predictive model. While we cannot determine this with certainty beforehand due to the complexities of machine learning algorithms, it is worth noting that previous studies [34, 37–40, 69] have successfully developed stable models using even smaller sample sizes. Based on this precedent, we believe that our chosen sample size will be adequate for the purposes of our investigation.

While convenient for logistical reasons, our use of convenience sampling introduces potential limitations. In employing this method, our sample may not be fully representative of the broader population due to potential biases associated with self-selection. This could limit the generalizability of our findings beyond the specific group of individuals who volunteered or were readily available. Nevertheless, the practicality of this approach expedites participant recruitment, allowing for extensive data collection in a controlled laboratory setting. Despite acknowledged limitations, we believe our targeted investigation will yield valuable insights into the relationships between empathy, physiological attributes, and immersive VR experiences within the context of our specific sample.

One of the primary challenges encountered in studies of this nature lies in establishing a reliable ground truth. We plan to do this with questionnaires. However, it is important to acknowledge that participants grading their own empathic states may introduce errors in the form of subjective biases. In light of this consideration, we will use two distinct questionnaires, one for measuring state empathy and another for trait empathy. This approach aims to minimize potential errors in our measurements in a way that may reveal some pattern of connections between the two.

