## Materials and methods

### Empathy elicitation using VR

Based on the narrative review on the use of VR for eliciting empathy [1], we have decided to immerse participants in 360º and three-dimensional (3D) virtual environment due to VR’s efficacy in eliciting empathic responses. Our choice of a 360º immersive setting is substantiated by comparative analyses demonstrating that it is equally or more effective at eliciting empathy compared to other approaches such as two-dimensional video/film [1, 34, 35], curriculum contents like workshops [36] or e-course materials [37], narrative-based perspective-taking exercises [9, 38], and text-based information [9, 35]. This effectiveness is observed immediately or with a lasting positive impact. Additionally, our decision to utilize a 3D level of immersion aligns with the findings of the review [1], which highlight the superior effectiveness of 3D immersion over two-dimensional.

During the VR experience, participants will adopt a first-person perspective, allowing them to observe the actors expressing emotions directly in front of them. This approach was chosen because research suggests that a first-person perspective is more effective than a third-person perspective, where the participant merely observes events happening among others [39, 40].

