### Study design and study population (Recruitment)

Convenience sampling will be employed to recruit participants from the general public. There will be no specific pattern for selecting respondents, as participants will be invited from various sources, including Jožef Stefan Institute employees, students from different university programs, and individuals from the general public. Potential participants will receive verbal or written invitations to participate in the study. Exclusion criteria will include individuals under 18 years of age, those diagnosed with epilepsy or heart conditions, individuals with health conditions or medication use that significantly impact their autonomic nervous system, and individuals with anxiety disorders (generalized anxiety disorder, panic disorder, social anxiety disorder, post-traumatic stress disorder). Inclusion criteria consist of a willingness to participate in scientific research and having normal vision, minor refractive errors, or the use of contact lenses.

We strive for age and gender-balanced groups, ensuring equal representation of male, female, and potentially other gender identities. Regarding education levels and study/work fields, our aim is to include individuals with diverse educational and professional backgrounds. We expect to have a participant pool of over 100 individuals.

Given that the primary objective of this study is to examine the association between changes in physiological attributes and empathy based on individual emotions, it falls under the category of a correlational study. A correlational approach will be employed to explore relationships among the aforementioned variables.

Ethical clearance for this study was obtained from the Research Ethics Committee at the Faculty of Arts, University of Maribor, Slovenia (No. 038–11-146/2023/13FFUM), as the participation of individuals in the research poses no risk of physical, psychological, legal, or social harm. Written informed consent was obtained from the actors prior to recording. Additionally, the individuals in this manuscript have given written informed consent (as outlined in PLOS consent form) to publish these case details. Participants will be informed about the study verbally, with the option to stop their participation at any point. Subsequently, they will receive a separate informed consent form prepared for them to sign prior to their participation in the study.

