**Fig 2 pone.0307385.g002:**
[figure not shown]
A participant watching videos via Pico Neo 3 Pro Eye headset in the process of collecting the dataset.

In addition to raw sensor data, the EmteqPRO system also provides derived variables. Integral to the emteqPRO system, the Emteq Emotion AI Engine uses data-fusion and machine learning algorithms to analyze the multimodal sensor data and recognize the user’s affective state. Comprising 7 different modules, the Emteq emotion AI engine provides affective insights for each recording. The ‘Data Insights’ feature in the SuperVision application, a web-based signal monitoring application, processes the data and generates a file containing 29 derived features, with 22 of them describing the seven modules [43]:

7 features describing heart-rate variability (HRV) derived from PPG;3 features describing breathing rate, derived from PPG [54];2 features describing expressions obtained from EMG;4 features describing arousal, obtained from both EMG and PPG [55];4 features describing valence, obtained from both EMG and PPG [55];1 feature describing facial activation that is determined through EMG;1 feature describing facial valence that is assessed using facial muscle data obtained through EMG.

Moreover, except the mentioned modules and the 22 features describing them, head activity is included as a feature, which indicates the percentage of the recording session during which head movement is detected. Additionally, dry EMG electrodes are strategically positioned over the zygomatic, corrugator, frontalis, and orbicularis muscles, which play a pivotal role in evaluating objective valence responses to stimuli. The EMG data hence yields four additional features, each delineating the activation of the corresponding muscles detected by their respective sensors. This activation is expressed as a percentage of the maximum activation observed during the calibration session.

The Empatica E4 wristband shares similarities with the emteqPRO system, as mentioned earlier, particularly in terms of its PPG sensor. Furthermore, it also provides derived variables, too. Thus, we will extract the following data from the Empatica E4 wristband (17):

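### The claim that about 100 participants suffice for a stable prediction model is unsupported: the article describes five of its six cited precedents as comparisons of stimuli or viewpoints, not as prediction models

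*Protocol article*

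**What the plan says.** The recruitment section gives the target: "We expect to have a participant pool of over 100 individuals". Under Strengths and limitations, the article notes that statistical models have established sample-size methods, says that an optimal size is hard to fix for machine learning, and continues: "we anticipate that approximately 100 participants will suffice to develop a stable predictive model". It admits that this cannot be known for certain in advance. It then offers one argument: "previous studies [34, 37–40, 69] have successfully developed stable models using even smaller sample sizes". On that precedent it concludes that the chosen size will be adequate.

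Five of these references appear elsewhere in the article. Under Empathy elicitation using VR, reference 34 is among the "comparative analyses demonstrating that it is equally or more effective at eliciting empathy compared to other approaches such as two-dimensional video/film [1, 34, 35"; references 37 and 38 continue the same list, for e-course material and narrative perspective-taking exercises. References 39 and 40 are cited there for the advantage of a first-person over a third-person viewpoint. Data analysis cites 38 again, for higher empathy scores after narrative exercises. Reference 69 is not described anywhere else.

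On the size of the task, Data collection says that the headset software "generates a file containing 29 derived features" and lists six wristband variables. Data analysis adds questionnaire data and features extracted from raw signals. The labels are the affective component of trait empathy and state empathy.

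**The concern.** A sample that was large enough to compare groups shown different material says nothing about whether a many-feature prediction model will be stable. If the references are what the article says they are, the one argument for the sample size does not bear on the question.

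Other statements in the article make borrowed precedent harder to rely on. The Introduction treats the link between physiological measures and empathy as unresolved, and Data collection says that no sensor measure of empathy is established.

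The prediction model is the study's main outcome in the Abstract. The Discussion aims at a reference standard for measuring empathy and at guiding therapy, and the Introduction names selection of people for roles. Readers with those uses in mind would rely on the word stable.

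**Working it through.** **The plan's own figure.** About 100 cannot be reproduced. The article gives no target performance, label prevalence, feature limit or formula for it. The check is therefore whether the stated basis supports the figure, and how the figure compares with a standard criterion.

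**Step 1: the precedent.**

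| Reference | How the article describes it elsewhere |
|---|---|
| 34 | 360-degree VR compared with two-dimensional film |
| 37 | 360-degree VR compared with e-course material |
| 38 | 360-degree VR compared with narrative exercises; effect of such exercises on empathy scores |
| 39, 40 | First- compared with third-person viewpoint |
| 69 | Not described |

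None of the five described references is presented as developing a prediction model.

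**Step 2: feature count (Data collection).** Headset modules: 7 + 3 + 2 + 4 + 4 + 1 + 1 = 22. Head activity and four muscles: 22 + 1 + 4 = 27. Six wristband variables: 27 + 6 = 33. With the stated 29 headset features the total is 35. Questionnaire and raw-signal features come on top, so 33 is a floor.

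**Step 3: shrinkage criterion, trait label.** Take a binary label and a target shrinkage S = 0.90: n = p / ((S − 1) · ln(1 − R² / S)), with R² on the Cox-Snell scale. The R² values are assumptions; the article gives none.

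- At R² = 0.2: ln(1 − 0.2/0.9) = −0.2513, so n = 33 / 0.02513, about 1,313.
- At R² = 0.3: ln(1 − 0.3/0.9) = −0.4055, so n = 33 / 0.04055, about 814.

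| Assumed R² | 0.1 | 0.2 | 0.3 | 0.5 | 0.7 |
|---|---|---|---|---|---|
| Participants needed, p = 33 | 2,802 | 1,313 | 814 | 407 | 219 |
| Parameters supported at n = 100 | 1.2 | 2.5 | 4.1 | 8.1 | 15.0 |

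The counterpart for a continuous trait score uses S = 1 + (p − 2) / (n · ln(1 − R²app)), where R²app is the apparent R². It gives about 2,627, 1,239, 775, 397 and 228 for the same R² values, so the choice of scale does not change the result.

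**Step 4: what eases the shortage.**

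- *Penalisation and correlated features.* I simulated ridge regression (n = 100, 33 features, 200 runs) with the best fixed penalty. At true R² of 0.1, 0.2 and 0.3, independent features gave an out-of-sample R² of about 0.01, 0.07 and 0.15. Five blocks with within-block correlation 0.6 and a shared signal, a favourable assumption, gave about 0.05, 0.14 and 0.24.
- *State label.* Four ratings per person (VR sessions) give about 400 rows. With intraclass correlation ICC, the effective number is 400 / (1 + 3·ICC): 250, 182 and 143 at assumed ICC of 0.2, 0.4 and 0.6. Of the table's requirements, these reach only that for R² = 0.7 (219), and only at ICC 0.2.

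**Step 5: precision at n = 100.** The Wilson interval is (x + z²/2n ± z·√(x(1 − x)/n + z²/4n²)) / (1 + z²/n). With observed accuracy x = 0.70, z = 1.96 and n = 100, this is (0.7192 ± 0.0919) / 1.0384, or 60% to 78%. It assumes a binary trait label and one independent prediction per person.

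**The case against.** The strongest reply is that the statement is an expectation in a limitations paragraph, openly uncertain, and that regression criteria do not transfer directly to machine learning. The hedge is real, and it is why the claim should be called unsupported rather than false. It does not rescue the precedent, which the article then uses to conclude that the size is adequate.

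Three stronger readings are tempting but go beyond the documents.

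- *That none of the six studies contains a model.* Reference 69 is not described, and a short citation shows only what a study was cited for at that point. The sources cannot be checked here.
- *That about 100 participants cannot yield a useful model.* The R², ICC and prevalence values are assumed, and the listed features overlap heavily: many derive from the same pulse and muscle signals. With such overlap a penalised model recovers much of the available signal.
- *That the model would do worse than predicting the mean.* That would follow from unpenalised least squares on all features. The article plans no such analysis; it plans tuned classifiers.

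It is also fair to say that feature selection and validation details may stand in a fuller plan. Their absence from an article is not the point here.

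**Conclusion.** The adequacy claim is unsupported on the article's own text. Its sole basis is precedent, and five of the six precedents are described there as something other than prediction models; the sixth is not described.

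The size of the gap is conditional. For the trait label with at least 33 features, about 100 participants miss the 10% shrinkage criterion at every assumed R² from 0.1 to 0.7, by a factor of roughly 2 at 0.7, 8 at 0.3 and 13 at 0.2. Correlated features, penalisation and clustered state ratings narrow the gap by amounts that depend on quantities the article does not give. None of them shows that the model will be stable, and the calculations do not show that it must be unstable.

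**What to change.** Under Strengths and limitations, delete the sentence that rests the sample size on references 34, 37 to 40 and 69, together with the statement of adequacy that follows from it. Say instead that about 100 participants support a proof-of-concept model. Give the expected precision, labelled as applying to the trait label and as depending on its assumptions; for example, observed accuracy of 70% would have a 95% interval of 60% to 78%. Claim stability only from performance estimated in participants who were not used to fit the model.

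The cost is a change of text and a less favourable stated claim. Enrolment and data collection do not change.
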